## **e. Data Analysis Objective 7**

For Objective 7, we will estimate the incremental cost to the provider (NDOH) of delivering each intervention per patient receiving the intervention, per patient achieving the primary outcome, and per clinic population eligible for the intervention. We will start with bottom-up costing of the resources utilized per patient served in the intervention clinics and recorded in the data sets collected under Objectives 1-5. Costs to be included are those identified in the cost analysis of the Adherence Guidelines we previously prepared for the NDOH[16]. These will be categorized as incremental or non-incremental to indicate whether they are additional budgetary expenses incurred by NDOH or a reallocation of existing resources. The quantity of each resource used by each enrolled patient will be estimated and then multiplied by the unit cost for that resource. Unit costs will be calculated from clinic invoices, NDOH and NHLS price lists, government salary scales, and other sources of actual costs incurred. We will use a top-down approach to estimate shared costs (e.g. clinic management) where necessary. We will closely follow the methods of the previously prepared cost analysis[16] to provide consistency of estimates. This analysis, in turn, follows the methods used in a number of papers we have published on the costs of HIV care in South Africa[17–19].

Once an average cost per patient receiving the intervention has been estimated, we will then estimate a cost per patient achieving the primary outcome (total cost of the intervention per site/total patients receiving the intervention), which is a preliminary measure of the cost-effectiveness of the interventions and can be compared to information from other published sources. We will also estimate the cost to offer the intervention to the full population in need at that site. The sum of these costs for all five interventions will indicate the cost to NDOH of implementing the minimum package at clinics of various sites. Finally, we will use the results of the evaluation to refine the previously completed cost analysis mentioned above[16], which will assist the NDOH to use the results for budgeting purposes.

If data collected on the TBHD cohort are sufficient to capture all resources utilized by the clinics for TB, hypertension, and diabetes care, we will use the same bottom-up cost methods to estimate the costs of care for these conditions per patient treated.

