- What is the effect of Enhanced Adherence Counselling on rates of being alive, in care, and virally suppressed within 3 and 12 months of intervention eligibility?

*Objective 5: Among HIV-infected patients in antiretroviral therapy programs who miss a scheduled appointment by 5 days,* ***evaluate the impact of Early Patient Tracing on retention in care****.*

Research questions:

- What is the effect of Early Patient Tracing on rates of returning to care by 3 and 12 months of tracing?
- What is the effect of Early Patient Tracing on rates of remaining in care by 12 months of tracing?

*Objective 6: For each clinic included in the study,* ***evaluate the overall impact of the Adherence Guidelines on patient outcomes****.*

Research questions:

- What is the effect of the package of interventions on patient retention in care overall?
- What is the proportion of population in need expected to benefit from the package of interventions?

*Objective 7:* ***Estimate the incremental and total cost of each of the interventions*** *listed above compared to standard of care.*

Research questions:

- What is the average cost per patient reached with the intervention?
- What is the average cost per successful outcome achieved?

*Objective 8:* ***Describe the current status of the cascade of care and adherence to treatment for tuberculosis, hypertension, and diabete****s, for the purpose of tailoring the minimum package of interventions to these conditions in the national rollout.*

Research questions:

- What is the prevalence of previously and newly diagnosed TB, hypertension, and diabetes among the population of patients presenting for care at primary health clinics, stratified by age, sex, and HIV status where possible?
- What proportion of diagnosed cases of these conditions are initiated on guideline-compliant treatment?
- What proportion of cases have satisfactory outcomes, based on current guidelines 12 months after diagnosis?
- For each condition, what proportion of patients are lost to care or discontinue treatment during the first 12 months after diagnosis?

Note that the impacts being assessed under Objectives 1-6 are the impacts of the interventions as implemented in the early phase of the national rollout of the guidelines. As is the case with program evaluations in general, results will reflect both intervention efficacy and implementation quality, which may in turn reflect the early learning stage of national policy implementation.

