| Overall impact (Objective 6) | Proportion of population in need at each clinic who achieve the short term primary outcomes defined above. | Proportion of population in need at each clinic who achieve the long term primary outcomes defined above. |
| Cost  (Objective 7) | Average cost per patient receiving an adherence intervention | Average cost per primary outcome achieved; average cost per 1000 patients receiving the observed mix of interventions |
| TB, hypertension, and diabetes (Objective 8) | For each condition, proportion of patients eligible for treatment who have 80% visit compliance in the first three months after diagnosis (S) and who achieve disease control at the six-month visit after diagnosis (L) as indicated in “Primary Care 101,” the NDOH’s guide for primary health clinic services[15]. The six-month visit will be represented by the visit closest to six months within the window of 5-8 months after diagnosis. The disease control indicators to be measured, with page references for Primary Care 101, are:  TB: cured or treatment completed indicated as the patient’s status at 6 months (page 57)  Hypertension: blood pressure controlled at 6-month visit, with control defined as < 140/90 (or 120/70–140/80 if diabetes, or <130/80 if CVD, heart failure or kidney disease) (page 74)  Diabetes: random glucose < 8 or HbA1c ≤ 7% at 6 month visit (page 71) | Among patients screened, prevalence of pre-diabetes elevated blood sugar (defined by Primary Care 101 as random glucose between 7.8 and 11) and pre-hypertension elevated blood pressure that require monitoring  Proportion of patients diagnosed with pre-diabetes or pre-hypertension who a) progress to diabetes and hypertension; or b) remain in care and receive appropriate monitoring for their condition over 12 months  Prevalence of diabetes, hypertension and TB among patients screened  Proportion of diagnosed patients initiated on appropriate treatment  Proportion of patients on treatment retained in care at 12 months. Loss to follow up will be defined as being 30 days late for a scheduled appointment.  Demographic and clinical characteristics of patients who do and do not achieve primary outcomes. |

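### Section 10e divides by patients receiving the intervention, so its cost per patient achieving the primary outcome is only the cost per recipient again

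*Protocol*

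**What the plan says.** Section 3c sets Objective 7: "Estimate the incremental and total cost of each of the interventions", relative to standard of care. Two separate research questions follow. One asks for the average cost per patient reached; the other asks "What is the average cost per successful outcome achieved".

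Table 3 (section 10a) keeps the two apart. The primary cost outcome is "Average cost per patient receiving an adherence intervention". The secondary cost outcomes are "Average cost per primary outcome achieved; average cost per 1000 patients receiving the observed mix of interventions".

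The opening sentence of section 10e also lists cost per recipient and cost per patient with the primary outcome as different quantities. Later the section says: "Once an average cost per patient receiving the intervention has been estimated, we will then estimate a cost per patient achieving the primary outcome". The formula then given in brackets is total intervention cost per site over total patients receiving the intervention: "cost per patient achieving the primary outcome (total cost of the intervention per site/total patients receiving the intervention".

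On the comparator, the Summary repeats the promise of costs relative to standard of care. Section 10e begins with "bottom-up costing of the resources utilized per patient served in the intervention clinics". It classes each cost as incremental or not according to whether it is new spending for the health department or existing resources redeployed.

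**The concern.** The bracketed ratio does not match its label. It repeats the cost per recipient that the same sentence says has already been estimated, so a listed secondary outcome has a formula that cannot produce it.

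Section 10e calls the result a preliminary cost-effectiveness measure and intends to set it beside published figures. A cost per recipient compared with published costs per outcome would look too cheap. The error also varies by intervention: two interventions with equal cost per recipient would appear equally cheap per success however much their success rates differ. Section 10g says the health department will use the results to target and budget the national rollout.

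The secondary concern is the comparator. Sections 4b and 4c give less visit burden and decongested clinics as goals of clubs and decentralized delivery. Section 4d notes that patients with detectable viral loads may already get extra counseling under standard care. Such savings and background costs show up only against comparison-clinic patients. Sorting intervention costs into new and redeployed spending does not measure them.

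**Working it through.** The protocol states no cost figure, so there is nothing to reproduce. The check is algebra plus the protocol's own planning rates.

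**Formulas.** Let C be total intervention cost, N the number of recipients, and p the proportion of recipients achieving the primary outcome.

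- Formula as written: C / N = c, the average cost per recipient. It does not contain p.
- Cost per outcome: C / (N × p) = c / p.
- Shortfall of the written formula: 1 − c / (c / p) = 1 − p.

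**Inputs.** The rates come from Table 4 (section 10b), which is sized on the short-term outcomes. Objective 1 states 60% without and 75% with the intervention. For the others, the stated 15-point difference is added to the baseline: 80% (Objectives 2 and 3), 52% (Objective 4), and 20–35% return with little or no intervention (Objective 5). The cost c is set to 1 unit, so only the ratios carry meaning.

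| Objective | p | Formula as written | Cost per outcome, 1/p | Understatement, 1 − p |
| --- | --- | --- | --- | --- |
| 1 | 0.75 | 1.00 | 1/0.75 = 1.33 | 25% |
| 2 and 3 | 0.80 + 0.15 = 0.95 | 1.00 | 1/0.95 = 1.05 | 5% |
| 4 | 0.52 + 0.15 = 0.67 | 1.00 | 1/0.67 = 1.49 | 33% |
| 5, baseline 35% | 0.35 + 0.15 = 0.50 | 1.00 | 1/0.50 = 2.00 | 50% |
| 5, baseline 20% | 0.20 + 0.15 = 0.35 | 1.00 | 1/0.35 = 2.86 | 65% |

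Table 4 also gives a 30% baseline for Objective 5 but words it as loss to follow-up. Read as 30% return, it gives p = 0.45, 1/0.45 = 2.22 and a 55% understatement, inside the range above.

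**Effect on comparisons between interventions.** Suppose tracing and decentralized delivery cost the same per recipient. The written formula gives them the same cost per success. At the planning rates, tracing would cost 0.95/0.50 = 1.9 to 0.95/0.35 = 2.7 times as much per success.

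**Comparator, read side by side.** The Summary and section 3c promise a comparison with standard of care. Section 10e names the intervention clinics as the starting point, defines incremental by budget status, and describes neither a comparison-arm cost nor a subtraction between arms. Section 9b lists visits, dispensing and laboratory results in a common set of fields for all patients in Cohorts 1–5, so the raw material for a comparison-arm cost is already being collected.

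**The case against.** The intended quantity is named correctly in section 3c, section 6, Table 3 and the first sentence of section 10e; only the bracket is wrong. Because it would return the number just calculated, an analyst would probably notice. Section 6 also limits cost per outcome to where data allow, and section 10e calls it preliminary. All of this supports reading the bracket as a drafting slip with a limited consequence. It does not make the formula right, and the contradiction remains.

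The multiples are open to challenge. Table 4 rates describe eligible patients, whereas the written denominator is recipients, and section 4 accepts that not every eligible patient at an intervention site may be enrolled in the intervention. The percentages therefore hold only if recipients succeed at the planned rates. That objection stands, and the sizes are illustrative.

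A reader might infer that costing is restricted to intervention clinics, so that no cost against standard of care can be obtained. The text does not support that. Section 10e presents the intervention clinics as the first step and then speaks of resources used by every enrolled patient. Section 6 refers to resource use per patient in care from the same data as the evaluation, which covers both arms. An incremental provider cost is also planned, on an accounting definition. Further detail may lie in the earlier cost analysis whose methods section 10e adopts, or in an analysis plan not at hand. What remains is that section 10e does not say how standard-of-care cost enters the promised comparison.

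**Conclusion.** The formula is wrong as written. It yields cost per recipient under the name of cost per outcome and contradicts section 3c, Table 3 and section 10e's own opening sentence. That conclusion rests on the text alone.

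Its size depends on the success rates. At the planning rates the understatement is 25%, 5%, 33% and 50–65% for Objectives 1, 2 and 3, 4 and 5 respectively. This assumes that recipients succeed at those rates, that the 15-point differences are gains, and that the short-term outcome is the one costed. For clubs and decentralized delivery the error would be small; for tracing, large.

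The comparator point is a secondary gap in specification and does not show that the comparison is impossible. One might also be tempted to cite 1/0.15 = 6.67 as the size of the error. That is the multiple for cost per additional success at a 15-point gain, and the protocol promises only average cost per outcome achieved.

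Cost per outcome is a secondary outcome of Objective 7. Randomization, sample size and the effectiveness analyses are not affected.

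**What to change.** 1. In section 10e, replace the bracket with total intervention cost divided by the number of patients achieving the primary outcome. State that successes are counted in the same patients whose costs form the numerator (recipients with recipients, or all eligible with all eligible). Say whether the short-term outcome, the long-term outcome or both are meant.
2. In the same section, state that the unit costs will also be applied to the resource-use data collected for comparison-clinic patients, and that the between-arm difference in mean cost will be reported for each cohort. The budget classification can stay as a separate presentation for planning.
3. Optionally, add the incremental ratio (difference in mean cost over difference in success proportion), with an interval from a bootstrap that resamples clinic pairs. This goes beyond what the protocol promises.

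The first change is one phrase and needs no new data. The second adds analysis but no new patient-level extraction; the team should check that the subset of clinics supplying unit costs covers what the comparison arm needs. The price is that cost per success will look higher than under the written formula, most of all where success is least common.

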Each of the interventions listed in Table 1 addresses a unique population of patients within a clinic, with the exception of interventions 4-6, which are substitutes for one another. For example, fast track initiation counseling is limited to patients eligible to start treatment; enhanced adherence counseling is limited to patients failing treatment; early tracing of missed appointments is limited to patients who are late for scheduled visits; and so on. While individual patients may become eligible for multiple interventions over the course of their care, the interventions will not serve overlapping cohorts of patients simultaneously. This will allow the impact of each intervention to be evaluated separately, as well as within the overall package.

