Each of the interventions, while implemented as a package of services, will be delivered to a unique population within each clinic: patients newly eligible for ART, patients stable on ART, patients with poor adherence, and patients lost from care. (The exception to this is patients who are stable on ART and could be provided with either decentralized medication delivery or adherence clubs, but not both.) This will allow us to estimate the effect of each intervention individually, in the context of implementation of the overall minimum package. During the early stages of implementation of the Adherence Guidelines it is possible that eligible patients at intervention sites might not all be enrolled in an intervention they are eligible for. In order to ensure that this evaluation does not by chance exclude eligible patients who are exposed to the interventions, enrolment at intervention sites will include not only those eligible for the intervention but also eligible patients who receive the intervention.

The following five interventions will be evaluated under this protocol. Each is described in detail in the National Adherence Guidelines[11]. (Note: Additional details about primary and secondary outcomes, eligibility criteria, sample size, and data sources are included in later sections of this protocol.)

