## **b. Adherence Clubs**

Adherence clubs comprise adherent and stable patients on ART who meet at facilities or identified locations in the community, in groups of up to 30 patients every two to three months to receive group counseling, have a clinical assessment, and receive the required supply of pre-packed medications. Adherence clubs are managed by lay staff at the health care facility with support from community health workers. The goal is to keep patients engaged in care and adherent to their medication by providing social support and facilitating medication delivery and treatment monitoring, while also reducing patient visit burden on the clinics[13]. The adherence guidelines SOP provides detailed instructions for establishing and running the clubs and for eligibility criteria and data collection.

| *Primary outcome:* | Proportion of patients eligible for participation in an adherence club who receive all medications within the first 4 months after eligibility |
| --- | --- |
| *Eligibility:* | All adult patients who meet the criteria for being stable on ART (on same ART treatment regimen for at least 12 months; most recent viral load taken in past 6 months, 2 consecutive viral loads undetectable ) OR where a clinician confirms eligibility as a stable patient |
| *Sample size:* | 576 (288 per arm; 24 per cluster) |
| *Data sources:* | Tier.Net; pharmacy records; club register; other registers or records that document services provided during the period of club observation |

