## **c. Data Analysis Objectives 1-5**

Our general analytic plan will be the same for each of Cohorts 1-5. We will begin with descriptive analyses of the characteristics of each of the cohorts stratified by intervention/non-intervention (comparison) cohorts. We will also look for differences within the randomized matched pairs. Because the data will be collected as part of a clustered design, the data analysis will need to account for clustering. For each primary outcome described above, we will conduct a crude analysis comparing the proportion of subjects with the outcome in the intervention and comparison arms. Next we will conduct an analysis for each outcome accounting only for clustering using generalized estimating equations (GEE) with an unstructured correlation matrix and clustering by treatment site. In all cases the outcomes are dichotomous and therefore we will calculate relative risks comparing the intervention to the comparison arms using a log link function and a binomial distribution. Next, should any imbalances between treatment groups be detected, we will adjust for those covariates in our GEE model. Finally, we will look for differences in the effects of the strategies by important baseline characteristics (e.g. size of the treatment population, rural vs. urban, province, etc.) using stratified analyses.

We note that because each of the interventions is targeted at a different population with the exception of decentralized medication delivery and adherence clubs, which would not be delivered to the same people at the same time, we can estimate the impact of each intervention separately, as only one of them will be delivered to each cohort within a clinic at any one time. Since some patients may participate in more than one intervention (e.g. fast track initiation followed by tracing), we will conduct a sub-analysis restricted to those who received only one intervention to look for the effects of each intervention by itself.

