## **d. Data Analysis Objective 6**

To provide an indicator of the overall (combined) effect of the package of interventions, we will analyze patient retention in care within intervention and comparison groups overall. We will include interaction terms between site and intervention to determine whether different packages of interventions produce different cumulative effects. Then, using available data on the population of patients eligible for each intervention at each site, we will weight the effects of the interventions in proportion to population to produce an estimate of the proportion of population in need expected to benefit from the interventions at each site.

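### The Objective 7 package cost adds full-population costs for adherence clubs and for decentralised delivery, so the stable ART patients they share are costed twice

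*Protocol*

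**What the plan says.** Section 10e (Data Analysis Objective 7) plans incremental costs to the provider on several bases, one of them "per clinic population eligible for the intervention". After the average cost per patient it adds: "We will also estimate the cost to offer the intervention to the full population in need at that site". It then aggregates: "The sum of these costs for all five interventions will indicate the cost to NDOH of implementing the minimum package". No adjustment for overlapping populations is given.

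Elsewhere the protocol treats two of the five interventions as alternatives for one group:

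- Section 3b (Rationale) says each intervention has its own patient population, "with the exception of interventions 4-6, which are substitutes for one another". In Table 1 these are adherence clubs, spaced and fast lane appointments, and decentralised delivery.
- The introduction to Section 4 says stable patients "could be provided with either decentralized medication delivery or adherence clubs, but not both".
- Section 10c names the same exception: "decentralized medication delivery and adherence clubs, which would not be delivered to the same people at the same time".
- Sections 4b and 4c give clubs and delivery the same eligibility text, beginning "All adult patients who meet the criteria for being stable on ART". Section 8b gives Cohorts 2 and 3 a single list of criteria.

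For Objective 6, Section 10d describes a site-level estimate of who stands to gain: "we will weight the effects of the interventions in proportion to population to produce an estimate of the proportion of population in need".

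**The concern.** A sum over interventions is a valid package cost only if each patient is charged for what he or she can receive. That works for initiation counselling, enhanced adherence counselling and tracing, which serve different patients at any one time. It fails for clubs and delivery: each is costed for all stable patients, although no patient is to have both. The protocol makes an exception for this pair when it separates effects, but not when it adds costs.

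The total is presented as what the health department would pay to implement the package. Section 10e also says the evaluation will refine an earlier cost analysis used for budgeting, and Section 10g names budgeting of the national rollout as a use of the results. A total that charges one group for two mutually exclusive services describes a package that no clinic delivers.

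**Working it through.** The protocol states no package cost, so there is no figure to reproduce. The check is algebraic.

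**Inputs from the protocol**
- Base for each intervention: the full population in need at the site (10e).
- Aggregation: plain sum over five interventions (10e).
- Eligible population for clubs and for delivery: the same stable ART patients (4b, 4c, 8b).
- Clubs and delivery are either/or (3b, 4, 10c).
- Population counts: clinic-level numbers eligible for each intervention (Table 2), so the stable group appears once under each.

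**Inputs not in the protocol (assumed)**
- N stable patients at a site; incremental unit costs cA (clubs) and cD (delivery); club share p.
- Costs proportional to patients, and both unit costs of the same sign.
- For this illustration only, every stable patient takes clubs or delivery.

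**Formulas**
- Rule as written: N·cA + N·cD = N(cA + cD).
- Each stable patient costed once: N[p·cA + (1−p)·cD].
- Ratio: R = (cA + cD) / [p·cA + (1−p)·cD].

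**Special cases**
- Equal unit costs c: R = 2c / c = 2 for any p.
- Even split, p = 0.5: R = (cA + cD) / [0.5(cA + cD)] = 2 for any unit costs.

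**Assumed range of unit-cost ratio, any split**

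| cA/cD | p = 0 | p = 0.25 | p = 0.5 | p = 0.75 | p = 1 |
|---|---|---|---|---|---|
| 0.5 | 1.5 | 1.714 | 2.0 | 2.4 | 3.0 |
| 1 | 2.0 | 2.0 | 2.0 | 2.0 | 2.0 |
| 2 | 3.0 | 2.4 | 2.0 | 1.714 | 1.5 |

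For example, with cA = 0.5, cD = 1 and p = 0.25, R = 1.5 / (0.125 + 0.75) = 1.5 / 0.875 = 1.714.

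**Effect on the package total.** If all components are positive and the stable component is doubled, the total rises by that component's share s of the correctly counted total: (1 + s) / 1. The share is not given. An assumed 20% gives +20%, and an assumed 80% gives +80%.

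**The case against.** The best reply is that the authors know of the overlap. They state it three times, and Table 3 lists as a secondary outcome a cost per 1000 patients at the mix of interventions actually seen, which does not double count. This is true, but that outcome is a separate quantity and Section 10e does not tie the package sum to it. The population in need might also be meant as already split between the two models. Nothing says so, and Section 10e and Table 2 both speak of patients eligible for the given intervention. Section 10e will follow the methods of an earlier cost analysis that is not at hand, so how that work handled the overlap is unknown.

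Other parts of the reply stand and limit the point:

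- **Direction.** A reader might infer that the package cost is necessarily overstated. The costs are incremental, and both models aim to relieve the clinics (4b, 4c). If an incremental cost is negative, the double count inflates a saving.
- **Size.** A reader might infer a flat 100% error. That needs equal unit costs or an even split, and purely per-patient costs. Section 10e includes shared costs estimated top-down, and a clinic running both models may bear set-up costs for each. Those are not double counted.
- **The two-option formula.** It serves as an illustration and is not the right costing rule. Spaced appointments target the same patients (3b, end of 4e), and Section 4 expects some eligible patients not to be enrolled, so the club and delivery shares need not add to 1.
- **Objective 6.** A reader might infer that its weights count stable patients twice. Section 10d does not fix how the weights combine or what the denominator is, and a proportion of a population is naturally a count of people. No distorted weights can be derived from that text; it supports only a request for clarification.

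**Conclusion.** The point holds for the Objective 7 package total. The stated rule, combined with the protocol's own eligibility and either/or statements, enters the stable group's per-patient incremental cost or saving twice. The absolute size cannot be computed from the protocol. Under the assumptions in the working, the stable-patient component is 2 times too large at equal unit costs or an even split, and 1.5 to 3 times too large across the assumed range.

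Severity is moderate. The sum is a derived figure. The primary cost outcome in Table 3, average cost per patient receiving an intervention, is unaffected, as are the comparisons and sample sizes of Objectives 1-5.

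**What to change.** In Section 10e, replace the plain five-way sum with these steps:

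1. Count the stable ART population at each site once.
2. Allocate it across clubs, decentralised delivery and any remainder (spaced appointments only, or not enrolled), using the mix observed at the intervention clinics.
3. Show all-club and all-delivery scenarios as a range.
4. Keep shared or set-up costs of running both models as separate items.
5. Add the costs of the other three interventions.

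In Section 10d, state as a clarification that stable patients enter the population-in-need denominator once.

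The cost is the rewording of two analysis paragraphs. Section 9b already collects club participation, medication pick-ups and dates of intervention services, so the observed mix should be obtainable without new data. Design, enrolment and the effectiveness analyses do not change.
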